**Investigation of the applicability of dry powder inhalation in patients with Parkinson's disease.**

---

The tests will be performed with a dummy test inhaler without any drug substance or excipient. Therefore, the risks of the test procedure itself are negligible. If a patient experiences unease or discomfort at any time during the test or the exercise inhalations, the test will be stalled immediately. Adverse events are defined as any undesirable experience occurring to a subject during the study, whether or not considered related to the test procedure. All adverse events reported spontaneously by the subject or observed by the investigator or his staff will be recorded. The possibility of the occurrence of serious adverse effects caused by use of the test inhaler is excluded by the use of a dummy test inhaler without drug or excipient.

**6.3 Follow-up of adverse events**

All adverse events will be followed until they have abated, or until a stable situation has been reached. Depending on the event, follow up may require additional tests or medical procedures as indicated, and/or referral to the general physician or a medical specialist.

**7. STATISTICAL ANALYSIS****7.1 Descriptive statistics**

Routine descriptive statistics of the subject characteristics (e.g. age, gender, weight, length, UPDRS III score) will be presented. The capability of the Parkinson's patients to generate a sufficiently large pressure drop will be described qualitatively.

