### **4.4 Sample size calculation**

The study is an observational study designed to obtain insight into the ability of Parkinson's patients to use a dry powder inhaler during *off* periods.

We based our sample size calculation on previous studies performed in Parkinson's disease. Canning et al (1997) evaluated exercise capacity, respiratory function and gait in 16 patients with mild to moderate Parkinson's disease. Guedes et al (2012) investigated the MIP and MEP in 26 patients with Parkinson's disease during *on* and *off* periods of levodopa compared to healthy volunteers. Seccombe et al (2011) recruited 19 patients with mild-moderate Parkinson's disease without respiratory disease and assessed ventilatory control. Since we only want to obtain insight into the ability of Parkinson's patients to use a dry powder inhaler during *off* periods, 15 patients valid for evaluation is sufficient.

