## 5. METHODS

### 5.1 Study parameters

#### 5.1.1 Main study parameters

The main study parameter is to determine if a Parkinson's patient can operate a test inhaler correctly during *off* periods, by testing if they can generate a sufficiently large airflow and volume through the test inhaler *theoretically* necessary to disperse a medicinal powder and transport the aerosol into the lower airways during an *off* period.

The parameter that describes whether or not a patient is capable of using the inhaler correctly is the (duration of the) pressure drop (s)he creates over the inhaler upon inhalation. For the Twincer™ a pressure drop between 2 kPa and 4 kPa is optimal. The main study parameter therefore is the capability of patients to create a pressure drop between 2 kPa and 4 kPa by using a test inhaler with the resistance comparable with the Twincer™. At least 11 out of 15 patients should be able to create a pressure drop between 2kPa and 4 kPa, when using the resistance comparable of the Twincer™.

From the pressure drops created with the three resistances, the following parameters (which give more insight in the inhalation profile) will be calculated:

- Peak and mean inspiratory flow rate (PIFR and MIFR).
- Acceleration towards peak inspiratory flow rate (flow increase rate: FIR).
- Inhaled volume.
- Total inhalation time.

The data obtained with the test inhaler (by using the three resistances) could be used to optimise the Twincer™ DPI for Parkinson's patients. Specific characteristics of the Twincer™ could be adjusted to what Parkinson's patients can do with a DPI, in order to realise a DPI with levodopa that Parkinson's patients can operate during the *off* phase. Such characteristics are for example the resistance, the dose and the emission profile. With this new knowledge we aim to develop a DPI with levodopa for Parkinson's patients.

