#### **5.5 Replacement of individual subjects after withdrawal**

Individual subjects will be replaced after withdrawal, until a number of 15 patients are reached.

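### Section 5.1.1 sets a numeric rule of 11 in 15 for the main parameter, but section 7.1 plans only a qualitative description, in different criterion wording and with no measure of uncertainty

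*Protocol*

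**What the plan says.** Section 5.1.1 of the protocol states: "The main study parameter therefore is the capability of patients to create a pressure drop between 2 kPa and 4 kPa", using the test inhaler at the Twincer-like resistance. It then gives a rule for the group: "At least 11 out of 15 patients should be able to create a pressure drop between 2kPa and 4 kPa". The outcome per patient is therefore binary, and the group result is a count out of 15.

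Section 7.1 is the only text under Statistical Analysis. It plans descriptive statistics of subject characteristics and then says of the main parameter: "The capability of the Parkinson's patients to generate a sufficiently large pressure drop will be described qualitatively". It mentions no count, percentage or interval, and it does not refer to the rule of 11 in 15.

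On size, section 4.4 says "We based our sample size calculation on previous studies performed in Parkinson's disease", cites studies of 16, 26 and 19 patients, and concludes that "15 patients valid for evaluation is sufficient". Section 5.5 holds the number at 15: "Individual subjects will be replaced after withdrawal, until a number of 15 patients are reached".

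**The concern.** A rule fixed in advance is useful only if the planned analysis produces the quantity that the rule is about. Here the rule needs a count of patients inside a pressure band, while the analysis section promises a verbal account of whether pressure drops were large enough. Three things are at stake.

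- **The rule.** Nothing in 7.1 obliges the report to state how many of the 15 met the criterion, or to set that number against 11.
- **The criterion.** The band in 5.1.1 has an upper limit. The wording in 7.1 has only a lower side.
- **The uncertainty.** A proportion from 15 patients is imprecise, and a qualitative description hides that. The result matters, because section 5.2 uses it to judge whether the Twincer needs adjusting for these patients.

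**Working it through.** **Inputs.** n = 15 (sections 4.4 and 5.5); threshold r = 11 (section 5.1.1). The protocol states no error rate, power, reference rate or precision target, so neither 15 nor 11 can be reproduced by calculation. What can be done is to describe what the rule implies.

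**Step 1: compare the criterion across sections.**

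| Section | Quantity | Limits |
|---|---|---|
| 5.1.1 | pressure drop, with its duration mentioned in brackets | 2 to 4 kPa |
| 5.2 | peak pressure drop | 2 to 4 kPa |
| 7.1 | pressure drop | large enough; no upper limit, no figure |

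A patient whose peak exceeds 4 kPa passes under 7.1 but falls outside the band in 5.1.1 and 5.2. One patient is worth 1/15 = 6.7 percentage points. For illustration, suppose 12 patients reach at least 2 kPa and two of them exceed 4 kPa. The count is 12/15 on the one-sided wording, which meets the rule. It is 12 − 2 = 10/15 on the band, which does not.

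**Step 2: uncertainty at the threshold.** The exact (Clopper-Pearson) 95% limits for x successes in n are

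- lower = 2.5% quantile of Beta(x, n − x + 1)
- upper = 97.5% quantile of Beta(x + 1, n − x)

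| Count | Percentage | Lower limit | Upper limit |
|---|---|---|---|
| 10/15 | 66.7% | 38.4% | 88.2% |
| 11/15 | 73.3% | 44.9% (Beta(11, 5)) | 92.2% (Beta(12, 4)) |
| 12/15 | 80.0% | 51.9% (Beta(12, 4)) | 95.7% (Beta(13, 3)) |

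At 11/15 the interval spans 92.2 − 44.9 = 47.3 percentage points. Other methods give a similar width: Wilson 48.0 to 89.1%, Jeffreys 48.3 to 90.3%, Agresti-Coull 47.6 to 89.5%. The Wald interval (51.0 to 95.7%) is unreliable at n = 15.

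**Step 3: how often the rule is met.** P(X ≥ 11) = Σ C(15, k) p^k (1 − p)^(15 − k), summed over k = 11 to 15. At p = 0.5 this is (1365 + 455 + 105 + 15 + 1)/32768 = 1941/32768 = 5.9%.

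| True proportion able | P(at least 11 of 15) |
|---|---|
| 50% | 5.9% |
| 60% | 21.7% |
| 70% | 51.5% |
| 80% | 83.6% |
| 90% | 98.7% |

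These true proportions are illustrative; the protocol names none.

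**The case against.** The strongest reply is that this is a small observational study whose stated aim is insight, and that a descriptive analysis suits it. Section 7.1 does not withdraw the rule in 5.1.1, and the word qualitatively may mean only that each patient is classed as able or not able, without a hypothesis test. The choice of interval method is the kind of detail a statistical analysis plan can hold. Much of this stands: no formal test is needed, and a missing interval method would not be a finding by itself. It does not remove the mismatch. Even a descriptive analysis of a binary outcome is a count and a percentage, and 7.1 promises neither while restating the criterion without its upper limit. An analysis plan that reported the count would be going beyond the protocol's own sentence.

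A reader might also infer stronger points that the protocol does not support.

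- **That meeting the rule leaves open that only a minority are able.** The protocol sets neither a 50% benchmark nor a 95% level. With both assumed, the statement holds only at exactly 11/15, since 12/15 or more excludes 50% by the exact interval. At 11 it is also borderline: the one-sided 95% exact lower limit is 48.9%, while a one-sided mid-p limit is 51.7%.
- **That 11/15 is a go/no-go decision, or a claim that most patients can use the inhaler.** No section says either.
- **That 15 patients is too few.** Section 4.4 relies openly on precedent and states no target that the design misses. That the cited studies were larger does not show a defect.
- **That the rule has been abandoned, or that the conclusion can be chosen freely afterwards.** The count in 5.1.1 is still in force and was fixed in advance. The room for choice comes from the criterion wording and from the missing commitment to report the count.

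**Conclusion.** The concern holds in a limited form. The analysis stated in 7.1 does not evaluate the rule stated in 5.1.1, does not use the same criterion, and gives no measure of uncertainty. This rests on the protocol's text alone and needs no outside assumption.

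The numbers show why it is worth correcting. A result that just meets the rule is 73.3% with an exact 95% interval of 44.9 to 92.2%, and a shift of one or two patients between criterion wordings can change whether the rule is met. The interval assumes 15 evaluable, independent patients with one yes/no outcome each; the 95% level is a reporting convention, not the protocol's. The point does not call the sample size or the descriptive character of the study into question. It should be corrected, but it is a matter of reporting and wording rather than of design.

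**What to change.** Replace the last sentence of 7.1 with text to this effect:

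> The number and percentage of patients who meet the section 5.1.1 criterion at the Twincer-like resistance will be reported with an exact (Clopper-Pearson) 95% confidence interval and compared with 11 of 15. Each patient's peak pressure drop at that resistance will be listed.

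Use one criterion in 5.1.1, 5.2 and 7.1. It should say whether the peak pressure drop or its duration decides, and whether exceeding 4 kPa counts as not meeting it. Without this, the interval would be placed on an undefined numerator.

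Optionally, add to 4.4 the precision that 15 patients give, for example 45 to 92% at 11/15, and note that a result of exactly 11/15 is imprecise.

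The cost is one line of analysis and some rewording, with no additional patients, visits or inhalations. The downside is that the stated conclusion becomes more modest.

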**8. ETHICAL CONSIDERATIONS****8.1 Regulation statement**

This study will be conducted according to the principles of the Declaration of Helsinki (version 9, October 2008, [www.wma.net](http://www.wma.net)) and in accordance with the Medical Research Involving Human Subjects Act (WMO).

**8.2 Recruitment and consent**

The study will be conducted in outpatient Parkinson's patients who are treated by a Neurologist of the Martini Ziekenhuis.

A Martini Ziekenhuis neurologist with Parkinson expertise will select possible suitable patients. Patients will be asked to participate by one of the researchers. The patient will receive patient information and an informed consent form from the researchers. The patients will have two weeks to consider their decision. The patient is allowed to contact

**Investigation of the applicability of dry powder inhalation in patients with Parkinson's disease.**

---

an independent physician for advice. The patient, neurologist and researcher must sign the informed consent form if consent is given. A stamped envelope will be enclosed by the patient information and informed consent form that can be used to send the informed consent form(s) to the investigator.

**8.3 Benefits and risks assessment, group relatedness**

This observational study has no specific benefits for the participating patients. The test inhaler that is used is a dummy, which means it contains neither drug nor excipient. Therefore, the patient will not inhale anything but air during the tests. Furthermore, the design of the test inhaler will exclude the possibility of inhalation of any inhaler part during the tests. The test inhaler is made of polypropylene, a tough and light weight material that does not wear down, to prevent the formation of small, inhalable particles (e.g. due to dropping, thumping or screwing on the resistance disk too tightly). This material is inert to ethanol. Therefore, parts of the inhaler can be cleaned and disinfected with this liquid without degradation of the material. Moreover, we have limited the study procedures to ten inhalations that will be performed in one session of maximally 30 minutes per patient.

In order to be able to test the ability to use a dry powder inhaler correctly during an *off* period, patients will be asked to postpone the intake of levodopa until they become *off*. Since the half life of levodopa is very short (60-90 min), we expect a patient will become *off* shortly after the planned levodopa dose. After they finish the test inhalations, they will take their levodopa. They will leave the hospital only when they are in an *on* period. Since all patients included are familiar with frequent *off* episodes, no new discomfort compared to other *off* episodes is expected. The timeframe between the morning levodopa dose and the postponed levodopa dose is expected to be shorter than the levodopa free period during the night. The patients are used to a levodopa free period and the effect of this levodopa free period on their motor function.

The objectives of the study are group related. Only when performed in Parkinson's patients during an *off* period, specific group related information on the inspiratory capacities of these patients could be obtained.

**8.4 Insurance**

As explained in the prior paragraph, the study is designed in such a way that the risks of participating are negligible. Therefore, a dispensation from the statutory obligation to provide insurance is requested. This request is enclosed in the research file (G1).

## **9. ADMINISTRATIVE ASPECTS AND PUBLICATION**

### **9.1 Handling and storage of data and documents**

Each patient will be assigned a Patient Allocation Number on registration. The Patient Allocation Number and the patient initials are to be entered on the Case Report Form. The investigator will retain all patient information for a period of at least 15 year from study completion. Data will be handled confidentially and if possible anonymously. Where it is necessary to be able to trace data to an individual subject, a subject identification code list will be used to link the data to the subject. The principal investigator will safeguard the key to the code. The handling of personal data will comply with the Dutch Personal Data Protection Act (in Dutch: De Wet Bescherming Persoonsgegevens).

### **9.2 Amendments**

Amendments are changes made to the research after a favourable opinion by the accredited METC has been given. All amendments will be notified to the METC that gave a favourable opinion.

### **9.3 End of study report**

The investigator will notify the accredited METC of the end of the study within a period of 90 days. The end of the study is defined as the last patient's visit.

In case the study is ended prematurely, the investigator will notify the accredited METC, including the reasons for the premature termination.

Within one year after the end of the study, the investigator will submit a final study report with the results of the study, including any publications/abstracts of the study, to the accredited METC.

### **9.4 Public disclosure and publication policy**

Upon completion of the study, appropriate measures will be taken to ensure suitable publicity. The trial will be added to the public registry prior to the start of the study at [www.trialregister.nl](http://www.trialregister.nl).

## 10. STRUCTURED RISK ANALYSIS

### 10.1 Potential issues of concern

#### 10.1.1 Previous use of the test inhaler

The test inhaler has been successfully used in another study; (ChildDPI-1) 'Investigation of the applicability of dry powder inhalation in school children' and has therefore been tested for technical and hygienic safety by the department of medical technique in the UMCG. Therefore, no problems due to the use of the test inhaler are expected.

#### 10.1.2 Analysis of potential effect.

The test inhaler is a dummy, which means it contains neither drug nor excipient. Therefore, the patient will not inhale anything but air during the tests. Furthermore, the design of the test inhaler will exclude the possibility of inhalation of any inhaler part during the tests. The test inhaler is made of polypropylene, a tough and light weight material that does not wear down, to prevent the formation of small, inhalable particles (e.g. due to dropping, thumping or screwing on the resistance disk too tightly). This material is inert to ethanol. Therefore, parts of the inhaler can be cleaned and disinfected with this liquid without degradation of the material. Moreover, we have limited the study procedures to ten inhalations that will be performed in one session of maximally 30 minutes per patient, including . explanation of the tests and the motor function (UPDRS section III) test.

In order to be able to test the ability to use a dry powder inhaler correctly during an *off* period, patients will be asked to postpone the intake of levodopa until they become *off*. Since the half life of levodopa is very short (60-90 min), we expect a patient will become *off* shortly after the planned levodopa dose. We prefer to start the inhalation tests when the UPDRS III motor score is at least 30 (out of 56). However, if the patient does not reach a UPDRS III motor score of 30 after a 2 hour waiting time, inhalations tests will start if the UPDRS III motor score is at least 25. After finishing the test inhalations, which will be performed in maximally 15 minutes, the patient will take his/her levodopa. Since all patients included are familiar with frequent *off* episodes, no new discomfort compared to other *off* episodes is expected. The timeframe between the morning levodopa dose and the postponed levodopa dose is expected to be shorter than the levodopa free period during the

night. The patients are used to a levodopa free period and the effect of this levodopa free period on their motor function.

### **10.1.3 Study population**

The study population consists of Parkinson's patients familiar with *off* periods.

### **10.1.4 Can effects be managed?**

Testing will take place in the hospital. In the hospital, a neurologist will be available in case of emergencies.

## **10.2 Synthesis**

Since participating patients are used to frequent *off* episodes, a levodopa free period and the effect of this levodopa free period on their motor function and since they will not inhale anything but air during the test, the risk of participation are negligible.

In order to reduce eventual risks, patient with significant lung disease are excluded.

**APPENDIX 1****The relationships between air flow resistance, flow rate, aerosol generation and lung deposition**

Dry powder inhalers can be considered as resistances to air flow. The driving force for an air flow ( $\Phi$ ) through an inhaler is a pressure drop ( $dP$ ), as obtained during inhalation when an under pressure in the lungs is created relative to the (ambient) air pressure by expansion of the lung volume. Because the air flow resistance of a powder inhaler is of the orifice type, there exists a linear relationship between the square root of the pressure drop across the inhaler and the flow rate:  $\sqrt{dP} = \Phi \cdot R$ , in which  $R$  represents the air flow resistance. From the equation it can be concluded that for a given pressure drop  $dP$ , the flow rate ( $\Phi$ ) increases when the air flow resistance ( $R$ ) decreases. Due to a high flow rate into the lungs, a large difference between lung pressure and ambient pressure (and thus, a high pressure drop across the inhaler) cannot be maintained.

For passive dry powder inhalers, the energy for aerosol generation is derived from the inhaled air flow through the inhaler. However, it is not the flow rate in absolute sense that determines the fine particle dose from a dry powder inhaler, but the flow rate in relation to the design of the inhaler. Effective inhalers convert the kinetic energy of the air flow into powder dispersion forces and they need high local air velocities within the inhaler for that rather than a high air flow rate through the inhaler. High flow rates through an inhaler are highly unwanted because they increase mouth and throat deposition of the aerosol and shift the deposition in the lungs to larger airways. The way to achieve high local velocities without having a high total air flow rate is to design narrow tortuous channels, turbulent zones or whirl chambers, which all contribute to a higher air flow resistance of the inhaler. Therefore, the prerequisite for operating a dry powder inhaler correctly is rather to achieve sufficient pressure drop across the inhaler than to achieve sufficient flow rate through the device. Currently marketed dry powder inhalers all perform well at a pressure drop between 2 and 4 kPa. They do have different air flow resistances, meaning that the aerosol can be delivered at flow rates varying between 45 and 110 L/min at the same pressure drop of 4 kPa across the device. This will result in different deposition patterns; deepest lung penetration and highest peripheral deposition fractions will be obtained for the inhalers with the highest air flow resistance. Therefore, a high air flow resistance is desirable, not only from deposition point of view, but as explained, also because they facilitate to generate a high pressure drop which also can be maintained over a longer period.

**APPENDIX 2 UPDRS (section III) motor examination****III. MOTOR EXAMINATION****18. Speech**

- 0 = Normal.
- 1 = Slight loss of expression, diction and/or volume.
- 2 = Monotone, slurred but understandable; moderately impaired.
- 3 = Marked impairment, difficult to understand.
- 4 = Unintelligible.

